### **10.4.1 Reporting of SAE**

#### **SAE Reporting to Parexel Pharmacovigilance Services via Electronic Data Collection Tool**

The Investigator must report any SAEs to the Parexel Clinical Studies Safety Centre within 24 hours of becoming aware of the event.

- The primary mechanism for reporting an SAE to Parexel Pharmacovigilance Services will be the EDC tool.
- If the electronic system is unavailable, then the site will use the paper SAE data collection tool (see next section) in order to report the event within 24 hours.
- The site will enter the SAE data into the electronic system as soon as it becomes available.
- The Investigator and the Sponsor (or Sponsor's designated agent) will review each SAE report and the Sponsor/Parexel will evaluate the seriousness and the causal relationship of the event to study treatment. In addition, the Sponsor (or Sponsor's designated agent) will evaluate the expectedness according to the reference document (Investigator Brochure or Summary of Product Characteristics). Based on the Investigator and Sponsor's assessment of the event, a decision will be made concerning the need for further action.
- After the study is completed at a given site, the EDC tool will be taken off-line to prevent the entry of new data or changes to existing data.

- If a site receives a report of a new SAE from a study subject or receives updated data on a previously reported SAE after the EDC tool has been taken off-line, then the site can report this information on a paper SAE form (see next section) or to the Sponsor by email.
- Specific phone numbers will be provided for each country involved in the study.
- Contacts for SAE reporting can be found in the table below.

#### **Suspected Unexpected Serious Adverse Reactions (SUSARs)**

Any AE that is serious, associated with the use of the study treatment, and unexpected (SUSAR) has additional reporting requirements, as described below.

- If the SUSAR is fatal or life-threatening, associated with study treatment, and unexpected, regulatory authorities and IECs will be notified within 7 calendar days after the Sponsor learns of the event. Additional follow-up (cause of death, autopsy report, and hospital report) information should be reported within an additional 8 days (15 days total).
- If the SUSAR is not fatal or life-threatening but is otherwise serious, associated with study treatment, and unexpected, regulatory authorities and IECs will be notified within 15 calendar days after the Sponsor learns of the event.

The Sponsor will notify the Investigators in a timely fashion of relevant information about SUSARs that could adversely affect the safety of subjects. Follow-up information may be submitted if necessary.

The Sponsor will also provide annual safety updates to the regulatory authorities and IECs responsible for the study. These updates will include information on SUSARs and other relevant safety findings.

#### **Reporting Serious Adverse Events via Paper Form (Back-up Method)**

The minimum information required for an initial report is:

- Name of person sending the report (e.g., name, address of Investigator);
- Subject identification (screening/randomisation number, initials, NOT subject name);
- Protocol number;

- Description of SAE;
- Causality assessment, if possible.

However, as far as possible all points on the SAE form should be covered in the initial report, or the completed SAE form itself must be emailed to the Parexel Safety mailbox. In addition, the event must be documented in the eCRF.

After receipt of the initial report, the safety centre will review the information and, if necessary, contact the Investigator, to obtain further information for assessment of the event. Parexel will be responsible for all information processing and reporting according to local legal requirements. Where necessary, Investigators will inform regulatory authorities and/or IEC/IRBs in their own countries.

*Parexel International*  
*SAE email: 255435\[contact]*  
*SAE answering service: [contact]*  
*Email: [[contact]](mailto:[contact])*  
  
*Medical Monitor: 255435\[contact]*

## **10.5 Appendix 5: Contraceptive Guidance and Collection of Pregnancy Information**

### **10.5.1 Definitions**

#### **Woman of Childbearing Potential (WOCBP)**

A woman is considered fertile following menarche and until becoming post-menopausal unless permanently sterile (see below).

If fertility is unclear (e.g., amenorrhea in adolescents or athletes) and a menstrual cycle cannot be confirmed before first dose of study treatment, additional evaluation should be considered.

Women in the following categories are not considered WOCBP:

1. Premenarchal
2. Premenopausal female with one of the following:

- Documented hysterectomy
- Documented bilateral salpingectomy
- Documented bilateral oophorectomy

NOTE: Documentation can come from the site personnel's review of the subject's medical records, medical examination, or medical history interview.

3. Post-menopausal female

- A post-menopausal state is defined as no menses for 12 months without an alternative medical cause.
  - A high follicle stimulating hormone (FSH) level in the post-menopausal range may be used to confirm a post-menopausal state in women not using hormonal contraception or hormonal replacement therapy (HRT). However, in the absence of 12 months of amenorrhea, a single FSH measurement is required.
- Females on HRT and whose menopausal status is in doubt will be required to use one of the non-oestrogen hormonal highly effective contraception methods if they wish to continue their HRT during the study. Otherwise, they must discontinue HRT to allow confirmation of post-menopausal status before study enrolment.

## 10.5.2 Contraception Guidance

### Male Subjects

Male subjects with female partners of childbearing potential are eligible to participate if they agree to ONE of the following during the treatment period and for at least 90 days after the last dose:

- Are abstinent from penile-vaginal intercourse as their usual and preferred lifestyle (abstinent on a long-term and persistent basis) and agree to remain abstinent.
- Agree to use a condom and consider contraception for non-pregnant when having penile-vaginal intercourse.

Male subjects with a pregnant or breastfeeding partner must agree to remain abstinent from penile-vaginal intercourse or use a male condom during each episode of penile penetration during the treatment period and for at least 90 days after the last dose.

No sperm donation is allowed from Day 1 to at least 90 days after receiving XVR011

### Female Subjects

Female subjects of childbearing potential are eligible to participate if they agree to use a highly effective method of contraception as described in the table below, consistently and correctly during the treatment period and for at least 90 days after the last dose.

No egg donation is allowed from Day 1 to at least 90 days after receiving XVR011

| Highly Effective Contraceptive Methods That Are User Dependent
Failure rate of <1% per year when used consistently and correctly.                                                     |
|-----------------------------------------------------------------------------------------------------------------------------------------------------------------------------------------------------------------------|
| Combined (oestrogen- and progestin-containing) hormonal contraception associated with inhibition of ovulation 
 
• Oral
 
• Intravaginal
 
• Transdermal
 
 |
| Progestogen-only hormonal contraception associated with inhibition of ovulation 
 
• Oral
 
• Injectable
 
                                                        |

|                                                                                                                                                                                                                                                                                                                                                                                              |
|----------------------------------------------------------------------------------------------------------------------------------------------------------------------------------------------------------------------------------------------------------------------------------------------------------------------------------------------------------------------------------------------|
| 
Highly Effective Contraceptive Methods That Are User Independent
 
Implantable progestogen-only hormonal contraception associated with inhibition of ovulation
 
 
• Intrauterine device (IUD)
 
• Intrauterine hormone-releasing system (IUS)
 
• Bilateral tubal occlusion
 
                      |
| 
Vasectomised Partner
 
A vasectomised partner is a highly effective contraception method provided that the partner is the sole male sexual partner of the WOCBP and the absence of sperm has been confirmed. If not, an additional highly effective method of contraception should be used.
                                                                               |
| 
Sexual Abstinence
 
Sexual abstinence is considered a highly effective method only if defined as refraining from heterosexual intercourse during the entire period of risk associated with the study treatment. The reliability of sexual abstinence needs to be evaluated in relation to the duration of the study and the preferred and usual lifestyle of the subject.
 |

NOTES:

 Typical use failure rates may differ from those when used consistently and correctly. Use should be consistent with local regulations regarding the use of contraceptive methods for subjects participating in clinical studies.

### 10.5.3 Pregnancy Testing

- WOCBP should only be included after a confirmed menstrual period and a negative highly sensitive urine pregnancy test or serum pregnancy test at screening (Day -1).
- Pregnancy testing should also be performed at the EOS (ie 28 days after the dose of study treatment), or at the time of ED, and as required locally.
- Pregnancy testing will also be performed whenever a menstrual cycle is missed or when pregnancy is otherwise suspected.

### 10.5.4 Collection of Pregnancy Information

#### Male Subjects With Partners Who Become Pregnant

- The Investigator will attempt to collect pregnancy information on any male subject's female partner who becomes pregnant while the male subject is in this study. This applies only to male subjects who receive XVR011.
- After obtaining the necessary signed informed consent from the pregnant female partner directly, the Investigator will record pregnancy information on the appropriate form and submit it to the Sponsor within 24 hours of learning of the partner's pregnancy. The female partner will also be followed to determine the outcome of the pregnancy. Information on the status of

the mother and child will be forwarded to the Sponsor. Generally, the follow-up will be no longer than 6 to 8 weeks following the estimated delivery date. Any termination of the pregnancy will be reported regardless of foetal status (presence or absence of anomalies) or indication for the procedure.

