| To evaluate the safety of a single intravenous XVR011 infusion in subjects hospitalised for COVID-19, compared to placebo                        | 
 
Proportion of subjects with Grade <math>\geq 3</math> treatment-related AEs within 28-day FU period
 
Proportion of subjects with AEs (all and serious) of any grade and independent of causality within 28-day FU period
 
Proportion of subjects with infusion-related reactions within 24 hours of treatment
 
Proportion of subjects with hypersensitivity reactions within 28-day FU period
 
 |
| Exploratory
To evaluate the effect of a single intravenous XVR011 infusion on disease biomarkers in subjects hospitalised for COVID-19 | 
 
Blood biomarkers (including but not limited to CRP, LDH, D-dimers, fibrinogen, absolute neutrophil count, lymphocyte count) at baseline (Day 1 pre-dose), on Days 2, 3, 4, 8, 15, 29 and on day of discharge
 
Optional blood sample for future exploratory biomarker testing at baseline (Day 1 pre-dose) and Day 3
 
                                                                                           |
| Additional evaluation of COVID-19 symptoms during the extended follow up period.                                                                 | 
 
COVID-19 related symptoms on Day 60 and Day 90
 
                                                                                                                                                                                                                                                                                                                                                                        |
| Characterise viral genotype                                                                                                                      | 
 
At baseline and Day 8
 
                                                                                                                                                                                                                                                                                                                                                                                                 |

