### **6.3.2 Part 2**

#### **6.3.2.1 Randomisation and Blinding**

Part 2 is a randomised double-blind study.

All subjects will be randomised centrally using an interactive response technology (IRT) to ensure that treatment assignment is unbiased and concealed from study subjects and the Investigator. The Investigator will be provided with usernames and passwords for randomisation purposes and to unblind the study treatment in case of emergency, where he/she considers it essential to know what treatment the subject was taking. The IRT will be designed to send a confirmation (by fax and/or notification email) to the site for every transaction performed by the Investigator.

Each subject will be assigned to one of the 2 arms of the study according to the randomisation schedule provided by the Parexel Informatic Manager utilising a validated computer program. Details of the procedure are described in the IRT Manual provided to all sites.

Subjects will be randomly assigned in a 2:1 ratio to receive study treatment (XVR011 or placebo). Stratification will be done at randomisation for country and for fully vaccinated/prior SARS-CoV-2 infection. Any EMA approved, FDA approved or WHO recommended vaccine will be taken into account. The original recommended vaccination frequency (either 1 or 2 injections depending on the vaccine) will be considered as fully vaccinated, i.e. the more recent recommendations for a booster shot are not required for the stratification definition.

The placebo IV bag will present the same external appearance with the same composition, except for the active ingredient. IV bag cover will be added to keep the blinding on the IV bag.

Randomisation data will be kept strictly confidential, accessible only to authorised persons, until the time of unblinding of the allocated treatment of all study subjects after locking the database upon termination of the study.

Subjects, Investigators and/or employees of the investigational site will remain blinded to each subject's assigned study treatment throughout the course of the study, unless in case of emergency.

In order to maintain this blind, an otherwise uninvolved third party (unblinded pharmacist) will be responsible for the reconstitution and dispensation of all study treatment and will endeavour to ensure that there are no differences in time taken to dispense following randomisation.

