### **8.3.5 Pregnancy**

- Details of all pregnancies in female subjects and, if indicated, female partners of male subjects will be collected after the study treatment and until the EOS.
- If a pregnancy is reported, the Investigator should inform the Sponsor within 24 hours of learning of the pregnancy and should follow the procedures outlined in Appendix 5, to collect information and determine the pregnancy outcome.
- Abnormal pregnancy outcomes (e.g., spontaneous abortion, foetal death, stillbirth, congenital anomalies, ectopic pregnancy) are considered to be SAEs.

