### **8.3.6 Adverse Events of Special Interest**

Adverse events of special interest include infusion related reactions (including hypersensitivity or anaphylaxis during or within 24 hours of XVR011 infusion and hypersensitivity reactions (other than IRR) and will be reported using the same process as for AEs).

All subjects should be closely observed under medical supervision during the XVR011 infusion administration and for  $\geq 120$  minutes thereafter. Vital signs, including blood pressure, heart and respiratory rates and body temperature will be evaluated for possible hypersensitivity reactions. Any type of ECG will be performed if a subject experiences cardiac symptom.

Emergency equipment, such as adrenaline, antihistamines, corticosteroids, and respiratory support (inhalational therapy, oxygen, and artificial ventilator) must be available. Medication for infusion reactions (IRR) should be available for immediate use.

As with any protein, infusion reactions (IRR)/hypersensitivity reactions may occur. This may vary from mild to moderate signs and symptoms but may also be a severe or life-threatening anaphylactic/anaphylactoid reaction. Signs and symptoms may include hypotension, tachycardia, bronchospasm, dyspnoea, oedema/angio-oedema, dizziness, headache, nausea, abdominal pain, fever, rash. Guidance in case of an infusion reaction based on severity of the reaction provided in Table 8–2.

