### **Female Subjects Who Become Pregnant**

- The Investigator will collect pregnancy information on any female subject who becomes pregnant while participating in this study. Information will be recorded on the appropriate form and submitted to the Sponsor within 24 hours of learning of a subject's pregnancy. The subject will be followed to determine the outcome of the pregnancy. The Investigator will collect any follow-up information on the subject and the neonate and the information will be forwarded to the Sponsor. Generally, follow-up will not be required for longer than 6 to 8 weeks beyond the estimated delivery date. Any termination of the pregnancy will be reported, regardless of foetal state (presence or absence of anomalies) or indication for the procedure.
- While pregnancy itself is not considered to be an AE or SAE, any pregnancy complication or elective termination of a pregnancy will be reported as an AE or SAE. A spontaneous abortion is always considered to be an SAE and will be reported as such. Any post-study pregnancy-related SAE considered reasonably related to study treatment by the Investigator will be reported to the Sponsor as described in Section 8.3.4. While the Investigator is not obligated to actively seek this information in former study subjects, he or she may learn of an SAE through spontaneous reporting.

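### Section 10.5.4 limits partner-pregnancy collection to male subjects who receive XVR011, a limit that a blinded Part 2 site cannot apply as written

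*Protocol*

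**What the plan says.** Protocol section 10.5.4, under the heading for male subjects, begins broadly: the Investigator tries to collect information on a pregnancy in the partner of any male subject while he is in the study. The next sentence narrows this: "This applies only to male subjects who receive XVR011". The Investigator must then obtain signed consent from the partner and send the form to the Sponsor within 24 hours of learning of the pregnancy.

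For Part 2, section 6.3.2.1 states that subjects, Investigators and site employees "will remain blinded to each subject's assigned study treatment throughout the course of the study, unless in case of emergency". The Sponsor is also blinded, apart from specific representatives outside the study team, and allocation is released only after database lock.

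The other pregnancy rules name no arm. Section 8.3.5 reads: "Details of all pregnancies in female subjects and, if indicated, female partners of male subjects will be collected after the study treatment". For female subjects, section 10.5.4 reads: "The Investigator will collect pregnancy information on any female subject who becomes pregnant while participating in this study".

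**The concern.** The rule depends on a fact that the person applying it does not have. In open-label Part 1 every treated subject receives XVR011, so the limit is harmless. In Part 2 it divides male subjects by allocation, and the Investigator has to act within a day while blinded.

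Two things are at stake. One is the blind: a site that takes the sentence literally has a reason to ask for the code, possibly with follow-up to Day 90 still to run. The other is even-handed safety collection: partner pregnancies in the placebo arm are out of scope on paper, and sites that guess or decide differently will produce incomplete records. Section 8.3.5 counts abnormal pregnancy outcomes as serious adverse events, so this information should not depend on allocation or on how a site reads one sentence.

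**Working it through.** No sample size, power or error rate is involved, so the check is a comparison of texts.

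1. **Who acts, and when.** Section 10.5.4 places the duty on the Investigator, requires the partner's consent first, and sets a 24-hour limit from learning of the pregnancy. The decision on whether the rule applies is therefore made at the site, during the study.

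2. **What that person knows.** Under section 6.3.2.1 the Investigator is blinded in Part 2. Section 6.3.2.2 provides for breaking the code in an emergency. A partner pregnancy is not in itself an emergency, and no other route to the allocation is given to the site.

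3. **What follows.** The condition in the restricting sentence cannot be evaluated when action is due. A site can ask for unblinding, collect nothing, or collect from every male subject. The text as restricted prescribes none of these for a blinded subject.

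4. **Is the restriction consistent with the rest of the protocol?**
   - Section 8.3.5 includes partner pregnancies where indicated, and names no arm.
   - The rule for female subjects in section 10.5.4 covers every female participant.
   - Inclusion criterion 6 ties male contraception to study treatment, for at least 90 days after the dose, in either arm.

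   The restricting sentence is the only pregnancy-collection rule that depends on allocation.

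5. **A likely origin (inference).** Section 10.5.3, in the same appendix, equates the end of study with 28 days after dosing. In Part 2 the end of study is Day 90, and Table 1-2 schedules pregnancy tests on Days 29, 60 and 90. The appendix appears not to have been fully adapted from Part 1.

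6. **Does section 8.3.6 have the same fault?** It describes infusion-related reactions as "hypersensitivity or anaphylaxis during or within 24 hours of XVR011 infusion". The texts that govern collection and analysis do not depend on arm:
   - Section 8.3.6 itself has all subjects observed.
   - Section 8.3.1 collects all adverse events from consent to end of study.
   - The endpoint in Table 3-2 is "Proportion of subjects with infusion-related reactions within 24 hours of treatment", under an objective of comparison with placebo.
   - Section 9.4.4 counts reactions within 24 hours of the start of infusion, by treatment group.
   - Table 9-2 puts everyone who started the study infusion in the safety set.

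   Here the drug name is loose wording for the study infusion, and nothing is left uncollected.

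**The case against.** The strongest reply is that a site need not unblind. Section 10.5.4 opens by covering any male subject's partner, so the site can collect for everyone and the limit can be applied after unblinding. Code breaks are confined to emergencies and are notified promptly to the Sponsor, so unblinding is not freely available. Section 8.3.5 already calls for a reported pregnancy to go to the Sponsor, with no arm named.

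Most of this stands. Collecting for all and filtering later is workable, and nothing forbids it. It is therefore wrong to infer that every case must end in either an unblinding or a lost record. But the protocol does not say this, and it would mean seeking consent from, and recording data on, partners whom the sentence puts out of scope if the subject had placebo.

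A second reply is that XVR011 may be shorthand for study treatment here, as it is in section 8.3.6. The sentence resists that reading: it expressly restricts the rule, and the restriction would do almost no work if every dosed male subject qualified.

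A reader might also infer that the infusion-reaction definition leaves the placebo rate undefined. The provisions in sections 8.3.1, 9.3 and 9.4.4 and in Table 3-2 show that it does not.

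**Conclusion.** The defect is real and narrow. In Part 2 the restricting sentence in section 10.5.4 cannot be applied as written without risking avoidable unblinding or collection that differs by arm, and it conflicts with the neighbouring pregnancy rules. This rests on the blinding rule in section 6.3.2.1 and on a partner pregnancy not being an emergency in itself.

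The size is small. Only male placebo subjects whose partners become pregnant during the study are affected. The protocol does not give that number, and few cases are expected. The whole placebo arm of 136 subjects is not the right measure, because it includes women and men to whom the rule will never apply. Nor would the placebo arm be without pregnancy data, since pregnancies in female subjects are collected in both arms. Partner pregnancy is not a listed Part 2 endpoint, so the primary analysis, the sample size, the type I error and the listed efficacy and safety endpoints are unchanged.

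**What to change.** In section 10.5.4, replace the restricting sentence with: *This applies to all male subjects who receive study treatment, irrespective of allocation.* This removes the dependence on allocation and brings the section into line with section 8.3.5 and the rule for female subjects. The cost is one sentence in an amendment and the follow-up of a few partner pregnancies in the placebo arm.

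As an optional tidy-up, section 8.3.6 could say study treatment infusion in place of XVR011 infusion; nothing in the analysis depends on it. Section 8.3.5 does not need to change for this point: its qualifier on when partner pregnancies are collected names no arm.
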